### Sample size calculation

The primary outcome for this trial is the WOMAC Pain score at 12-months post-operative. The trial is powered to allow the THR and TKR groups to be analysed separately. Three hundred patients listed for TKR are being recruited into the study, and 150 patients will be randomised to the intervention arm and 150 to the standard care arm. The same number of patients listed for THR are being recruited and randomised. This sample size will provide 90% power to detect a difference of 0.5 standard deviations on the WOMAC Pain Scale with a two-sided 1% significance level, and allows for a 20% dropout rate. Previous research suggests standard deviations of around 17 mm on the WOMAC Pain Scale before surgery[44]. Hence a difference between the treatment groups of 0.5 standard deviations equates to a difference of approximately 8-9 units on the WOMAC Pain Scale (0-100 scale).

### Statistical analysis

In terms of generalisability, the characteristics of those successfully recruited into the trial will be compared with those who were eligible but declined to participate. A CONSORT diagram [45] will summarise participant flow through the study, documenting invitation and recruitment, receipt of intervention or standard care as allocated, and collection of data. To check for balance between the groups, participants in the intervention and standard care arms will be described separately in terms of demographic, stratification/minimisation variables, and baseline measures. The percentage of participants not providing primary and secondary outcome data at each of the follow-up stages will be reported for each trial arm. Factors associated with missing data (such as demographics and values of primary and important secondary outcome variables at baseline) will be explored.

Analysis will consider TKR and THR separately. The primary analysis will be implemented using a multivariable generalised linear model to investigate between-group differences in mean WOMAC pain score at 12 months follow-up, adjusting for minimisation variables and baseline value of the primary outcome. The type of model will depend on the distribution of the WOMAC pain score data. The primary analysis will be conducted on an intention-to-treat (ITT) basis without imputation. However, sensitivity analyses will inform the interpretation of the primary analysis. These will include an estimate of between-group difference for the primary outcome using a per-protocol analysis. In addition, the effect of missing primary outcome data will be investigated using multiple imputation methods and random effects regression models will be used to investigate any clustering of outcomes by surgeon.

The same general approach will be followed for analysis of secondary outcome measures. For additional exploratory analyses, data will be considered within each treatment group separately and so treated as two cohort studies. Analyses will examine the impact of potential risk factors, specified a priori (see section on potential prognostic factors), on pain severity at 12-months post-operative independent of any treatment effects.

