##### Intervention group

The intervention group receives the same anaesthetic and analgesic regime as the standard care group, plus an intra-operative local anaesthetic wound infiltration. The local anaesthetic mixture consists of 60 mls of 0.25% bupivacaine with 1 in 200,000 adrenaline. If the patient is below 60 kg or particularly frail, the volume of injectate is reduced to 50 mls or lower if necessary. The surgeon injects the anaesthetic mixture into the joint capsule and short external rotators, fascia, fat and subcutaneous tissue.

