##### Intervention group

The intervention group receive the same anaesthetic and analgesic regime as the standard care group, plus an intra-operative local anaesthetic wound infiltration. The local anaesthetic mixture is the same as described for THR participants. The surgeon injects the anaesthetic mixture into the posterior capsule, medial and lateral capsule, fascia and muscle, and subcutaneous tissues.

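### The per-protocol sensitivity analysis is not a randomised comparison and can be biased; a complier-average effect would answer the treatment-received question better

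*Protocol article*

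**What the plan says.** The Statistical analysis section sets the primary analysis set: "The primary analysis will be conducted on an intention-to-treat (ITT) basis without imputation". It continues: "However, sensitivity analyses will inform the interpretation of the primary analysis". Per-protocol is the first of these: "These will include an estimate of between-group difference for the primary outcome using a per-protocol analysis". Multiple imputation for missing primary outcomes and random effects models for clustering by surgeon follow. The same section plans a CONSORT diagram that records, among other things, "receipt of intervention or standard care as allocated, and collection of data".

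The Intervention section defines the contrast. For hips: "The intervention group receives the same anaesthetic and analgesic regime as the standard care group, plus an intra-operative local anaesthetic wound infiltration". The text for knees has the same content. No sham injection is described for either joint. The hip text also provides for a smaller volume: "If the patient is below 60 kg or particularly frail, the volume of injectate is reduced to 50 mls or lower if necessary". The knee text adopts the same mixture.

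Under Randomisation, surgeon and anaesthetist learn the allocation when the operation begins. Participants, assessors and ward staff remain blind.

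**The concern.** A per-protocol comparison keeps its randomised basis only if the same kind of patient is removed from both arms. That cannot be done here for the main departure of interest, an intervention patient who is not infiltrated. Nobody in the control arm is offered the infiltration, so a control patient who would have missed it looks like any other control and stays in the analysis.

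The decision not to infiltrate is also made by people who know the allocation and can see the patient's condition. Non-receipt may therefore be related to prognosis, although the article does not show that it is.

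At stake is how the result is read. WOMAC pain is scored so that higher is better (Primary outcome measure). If non-recipients have the poorer outlook, dropping them raises the intervention mean and moves the estimate towards benefit, even when there is no effect. If they have the better outlook, the shift goes the other way. An analysis meant to help interpret the primary result should not carry an error of unknown sign when the trial's own data allow one that does not.

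**Working it through.** **Inputs from the protocol article (Sample size calculation).** 150 per arm for each joint; 20% dropout; 0.5 SD difference; two-sided 1% level; 90% power; SD about 17, a pre-operative figure. The target is 0.5 × 17 = 8.5 units, in line with the article's 8–9.

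**Plan's own figure.** n per arm = 2(2.576 + 1.282)² / 0.5² ≈ 119.1, so 120 evaluable; 120 / 0.8 = 150 randomised. The stated size is reproduced and nothing in it is wrong. The check below uses 120 per arm.

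**Assumptions, not in the article.** f = share of the intervention arm not infiltrated and excluded, 2–10%. d = how much worse their expected WOMAC pain is than that of the other patients, 0.5–1 SD, or 8.5–17 units.

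**Formulae.** Let μ be the untreated mean of patients who would receive the infiltration if offered it, and τ its effect in them. Assume that no control is infiltrated.

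- Intervention arm after exclusion: μ + τ
- Control arm, nobody removed: μ − f × d
- Per-protocol difference: τ + f × d, so the bias is f × d
- ITT difference: (1 − f) × τ
- Complier-average causal effect (CACE): ITT / (1 − f) = τ

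**Bias in the per-protocol estimate.**

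| f | d | f × d (units) | Share of 8.5 |
|---|---|---|---|
| 2% | 8.5 | 0.17 | 2% |
| 5% | 8.5 | 0.43 | 5% |
| 10% | 8.5 | 0.85 | 10% |
| 10% | 17 | 1.7 | 20% |
| any | 0 | 0 | 0% |

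**Simulation check** (120 per arm, SD 17, f = 10%, 8,000 trials per row).

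| d | True effect | ITT | Per-protocol | CACE |
|---|---|---|---|---|
| 8.5 | 0 | −0.02 | 0.83 | −0.03 |
| 8.5 | 8.5 | 7.64 | 9.34 | 8.48 |
| 0 | 8.5 | 7.66 | 8.50 | 8.51 |

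The formulae give 0.85 for per-protocol in the first row. In the second they give 7.65 (ITT), 9.35 (per-protocol) and 8.5 (CACE). The simulation agrees within sampling error.

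**Precision.** At f = 10% and d = 17, a simulation of 20,000 trials gave a standard error of 2.29 for per-protocol and 2.53 for the CACE, a ratio of about 1.10.

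**The case against.** The case for leaving the plan alone has weight.

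- **Role.** ITT is primary and per-protocol is one of several supporting analyses. This stands, and it keeps the point minor.
- **Definition.** The article does not define the per-protocol set. That is commonly left to the analysis plan or full protocol, so its absence is no fault. The concern does not depend on it: any set that excludes uninfiltrated intervention patients has the problem.
- **Which arm loses patients.** A reader might infer that exclusions fall in the intervention arm alone. The article does not say so. Controls can depart from standard care (for example the femoral block in knees, paracetamol or patient-controlled analgesia) or be given an infiltration, and the plan records "receipt of intervention or standard care as allocated". This stands. But removing controls for those reasons removes a different group, not the counterparts of the uninfiltrated patients, so comparability is not restored.
- **Frailty and volume.** A reader might take the smaller volume for light or frail patients as evidence that the excluded patients are the frail ones. That reduction is itself part of the protocol, so on a plain reading these patients adhered and stay in. Nothing in the article ties complete non-receipt to 12-month pain. This stands: bias is possible, not demonstrated.
- **Size.** Both f and d are assumed. Adjustment for baseline pain and the minimisation variables would shrink d as far as they explain it. Even 1.7 units is 1.7 / 2.29 = 0.74 of a standard error. This stands.
- **Value of the alternative.** With one-sided non-receipt the CACE is essentially the ITT estimate divided by the receipt rate, so it adds little evidence against the null. That is true, and it is also the merit: it cannot suggest a benefit that the randomised comparison does not show.

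**Conclusion.** The point holds as a minor matter of analysis choice. In this add-on design without a described sham, and with operators who know the allocation, a per-protocol comparison that excludes uninfiltrated intervention patients is not a randomised comparison and can be biased by f × d. Under the assumed ranges this is about 0.2–1.7 units, or 2–20% of the 8.5-unit target. It favours the intervention only if the excluded patients have the poorer prognosis, and it vanishes if non-receipt is unrelated to prognosis. The figures also rest on an SD of 17, which the article quotes from before surgery, and on no controls being infiltrated.

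The article does not support a claim that the per-protocol result will be biased or that the trial's conclusion is in danger. The ITT primary analysis is untouched, and the article contains no contradiction or numerical error on this point.

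**What to change.** For TKR and THR separately, add a complier-average causal effect on 12-month WOMAC pain. Use randomised arm as the instrument for recorded receipt of any infiltration, and adjust for the minimisation variables and baseline WOMAC pain as in the primary model. Two-stage least squares is the simplest implementation. Count a volume reduced as the protocol permits as receipt. Name this as the treatment-received sensitivity analysis and keep per-protocol as descriptive only. Report the number not infiltrated in the intervention arm and the number infiltrated in the control arm, so that readers can judge f.

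The cost is a few lines of analysis, because receipt as allocated is already to be documented for the CONSORT diagram. The interval is slightly wider (standard error about 2.5 against 2.3 units at 10% non-receipt). The estimate also needs an exclusion restriction, meaning that allocation affects pain only through receipt of the infiltration; patient blinding makes this plausible. If some controls are infiltrated, it must further be assumed that nobody would do the opposite of their allocation under both arms.

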### Health economic analysis

The aim of the economic evaluation is to compare from a societal perspective the costs and effects of the intervention compared to standard care. Resource use in relation to joint replacement is collected from the date of operation until the end of the trial. Health service resource use is valued using the hospital finance department data, as well as routine UK data sources. Patient and informal carer resource use is valued using self-report and routine data sources. The analysis will consider TKR and THR participants separately. The analysis will first estimate the between group differences in mean costs using bootstrapping techniques to obtain bias corrected confidence intervals if the data are skewed. Then, incremental cost effectiveness between the two arms of the trial will be estimated using the WOMAC Pain score and the EQ-5 D to calculate Quality Adjusted Life Years (QALYs) for this population during the trial period. These results will be presented as incremental cost-effectiveness ratios and cost-effectiveness acceptability curves, derived used bootstrapping techniques. These will show the probability of the intervention being cost-effective at a range of 'willingness to pay' threshold levels.

The net monetary benefit statistic, using the difference in costs and the difference in QALYs between the two arms of the trial, will also be calculated for the different values of the societal willingness to pay for a year of life. In addition, because of the number of important secondary outcomes, a cost consequence analysis will be conducted in which the difference in costs and the difference in effects between the two arms of the trial are presented in tabular form. Sensitivity analysis will then be conducted to take account of uncertainty and imprecision in measurements, and will include multiple imputation models for missing values. All these analyses will be on an ITT basis and will adjust for minimisation variables.

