### Randomisation

Before participants undergo surgery, they are randomised to either the standard care group or the intervention group. Randomisation is conducted by means of a computer-generated code, administered centrally and communicated via the internet (through the Bristol Randomised Trials Collaboration). Randomisation is stratified by operation site (TKR/THR) and minimised by baseline joint pain severity and surgical approach. The operating surgeon and anaesthetist are blind to the results of randomisation until the beginning of the operation, when they are informed of treatment allocation by a member of the research team who is not involved in outcomes assessment. The study participants, research nurses involved in recruitment and assessment, and clinical staff involved in the care of study participants are blind to treatment allocation throughout the study.

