### Assessment times

Participants are followed-up for 12-months after surgery. Assessments are conducted pre-operatively, daily during the hopsital stay, and then at 3-months, 6-months and 12-months post-operative. Outcomes are assessed using self-report questionnaires, joint examinations, analysis of x-rays, pressure algometry and extraction of data from hospital records.

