### Potential prognostic factors

A number of possible potential prognostic factors are also being recorded, including socio-demographic factors, medical comorbidities, structural joint damage, health-related quality of life and psychosocial factors. The EQ-5D[38] is being used as a measure of health-related quality of life and the following questionnaires are being used to assess psychosocial factors: Hospital Anxiety and Depression Scale [39], Pain Self-Efficacy questionnaire[40], Illness Perceptions Questionnaire-Revised [41] and the Brief COPE [42].

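### The covariate rule for the economic analyses names the minimisation variables but not baseline EQ-5D, so a chance difference in baseline utility can carry partly into the QALY results

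*Protocol article*

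**What the plan says.** All references are to the protocol article.

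- **Health economic analysis**, covariates: "All these analyses will be on an ITT basis and will adjust for minimisation variables". No other covariate is named there.
- **Health economic analysis**, effect measure: incremental cost-effectiveness "will be estimated using the WOMAC Pain score and the EQ-5 D to calculate Quality Adjusted Life Years (QALYs) for this population during the trial". Net monetary benefit and the acceptability curves use the same QALY difference, and TKR and THR are taken separately.
- **Randomisation**: "Randomisation is stratified by operation site (TKR/THR) and minimised by baseline joint pain severity and surgical approach". EQ-5D is therefore not a minimisation variable.
- **Statistical analysis**, primary outcome: the model is fitted "adjusting for minimisation variables and baseline value of the primary outcome". For secondary outcomes: "The same general approach will be followed for analysis of secondary outcome measures".
- **Potential prognostic factors**: "The EQ-5D[38] is being used as a measure of health-related quality of life". This implies a pre-operative measurement, but no time point is given.
- **Assessment times**: "Assessments are conducted pre-operatively, daily during the hopsital stay, and then at 3-months, 6-months and 12-months post-operative". The article does not say at which of these the EQ-5D is completed.

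**The concern.** The clinical rule has two parts: the minimisation variables and the baseline value of the outcome. The economic section states the first part and does not repeat the second.

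The second part matters at least as much for QALYs. In an area-under-the-curve QALY, baseline utility is the first point on the curve, so it is part of the outcome itself. It also predicts later utility. If the arms differ by chance in baseline utility, some of that difference appears in the QALY contrast although treatment did not cause it. Every summary built on the contrast inherits it. The article's Discussion ties implementation to the intervention being both effective and cost-effective, so the precision of this result has practical weight.

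**Working it through.** **1. Number analysed.** The Sample size calculation section gives 0.5 SD, 90% power, two-sided 1% and 20% dropout.

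- n per arm = 2 × (2.576 + 1.282)² / 0.5² ≈ 119.03, rounded up to 120.
- Allowing for dropout: 120 / (1 − 0.20) = 150 per arm.

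This reproduces the stated 150 per arm for each joint. I use 120 analysed per arm below.

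**2. Weight of baseline utility in the QALY.** The article gives no QALY formula. I assume a trapezoidal area under the curve with EQ-5D at 0, 3, 6 and 12 months, which are the non-inpatient assessment times. The weights at 0, 0.25, 0.5 and 1 year are 0.125, 0.25, 0.375 and 0.25, which sum to 1. Baseline therefore has weight 0.125 and follow-up 0.875.

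**3. Share of an imbalance that carries over.** Let b be the slope of follow-up utility on baseline utility, with the minimisation variables held fixed.

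Carry-over = 0.125 + 0.875 × b

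| b (assumed) | Carry-over |
|---|---|
| 0.2 | 0.300 |
| 0.4 | 0.475 |
| 0.6 | 0.650 |

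**4. Size of a one-SE imbalance left after adjusting for the minimisation variables.** Let ρ be the correlation of baseline utility with those variables.

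SE = SD × √(2/120) × √(1 − ρ²), where √(2/120) = 0.1291

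- SD 0.30, ρ = 0: 0.0387
- SD 0.30, ρ = 0.7: 0.0387 × 0.714 = 0.0277
- SD 0.20, ρ = 0.7: 0.0258 × 0.714 = 0.0184

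**5. Shift in the QALY difference = carry-over × SE.**

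| SD | b | ρ | Shift |
|---|---|---|---|
| 0.20 | 0.2 | 0.7 | 0.300 × 0.0184 = 0.006 (smallest) |
| 0.30 | 0.4 | 0.7 | 0.475 × 0.0277 = 0.013 |
| 0.30 | 0.4 | 0 | 0.475 × 0.0387 = 0.018 |
| 0.30 | 0.6 | 0 | 0.650 × 0.0387 = 0.025 (largest) |

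Net monetary benefit moves by the willingness-to-pay threshold times the shift, that is by 0.6% to 2.5% of the threshold per patient.

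**6. Sensitivity to the EQ-5D schedule.** With SD 0.30, b = 0.4 and ρ = 0, the shift is 0.018 for 0/3/6/12 months. It is 0.021 for 0/6/12 months (baseline weight 0.25) and 0.027 for 0/12 months (weight 0.5). Sparser assessment makes baseline count for more.

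**7. How often.** Under a normal approximation, an imbalance of at least one SE in either direction occurs in about 32% of comparisons. With TKR and THR analysed separately on different patients, the chance in at least one joint is 1 − 0.683² ≈ 53%.

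**The case against.** A reader might infer that the economic analysis adjusts for the minimisation variables only. The article does not say so; exclusivity is read from silence. The Statistical analysis section extends its general approach to secondary outcomes, and cost-effectiveness is listed among them, so baseline adjustment may be intended. That reading is open. Against it, the economic section has its own explicit rule for all its analyses and leaves this element out. The text supports two readings, and one sentence would settle the matter.

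A reader might also infer that a utility imbalance passes straight into the cost-effectiveness ratio. It does not. Baseline pain is balanced by minimisation and adjusted for, which removes the part of the imbalance that tracks pain. Only some of the remainder carries over (0.30 to 0.65 in the working). EQ-5D is broader than joint pain, however: even at a correlation of 0.7, about 71% of the standard error remains.

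Nor is this bias. Under randomisation the imbalance has expectation zero and belongs to the sampling variation that the bootstrap describes. What is lost is precision, and protection against an imbalance that happens to occur. This is the ordinary reason for adjusting WOMAC Pain for its baseline.

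It is tempting to add that the infiltration is cheap, so small QALY differences will decide the conclusion. The article gives no expected cost or QALY difference, and its societal perspective takes in later care, time off work and informal care. That claim is unsupported.

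Finally, a condensed article may leave the QALY formula, EQ-5D schedule and regression form to a fuller plan, and I do not criticise their absence. The covariate set is different, because the article does state it.

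**Conclusion.** The point holds as a free improvement, not as an error that invalidates the analysis. The covariates stated for the economic analyses do not include baseline EQ-5D, while the primary clinical analysis includes its outcome's baseline value. If QALYs are an area under the EQ-5D curve, a one-SE chance imbalance in baseline utility, after allowing for absorption by the minimisation variables, would move incremental QALYs by about 0.006 to 0.025.

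That range rests on assumptions from outside the documents: the EQ-5D SD, the slope, the correlation, assessment at 0, 3, 6 and 12 months, and a linear model. Only the 120 analysed per arm follows from the article's own figures. Whether a shift of this size would change the cost-effectiveness conclusion cannot be judged from the article.

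**What to change.** Keep the existing sentence in the Health economic analysis section and add, for example:

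> In line with the clinical analysis, QALY differences, and the incremental cost-effectiveness ratios, net monetary benefit and acceptability curves built on them, will also be adjusted by regression for baseline EQ-5D utility, with the adjustment repeated within each bootstrap replicate.

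Confirm at the same time that the EQ-5D is completed pre-operatively, as the Potential prognostic factors section implies.

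The cost is one sentence and one covariate that appears to be collected already. Sample size, recruitment and assessments do not change. An area-under-the-curve QALY needs the baseline value anyway, so the covariate excludes no further patients. Fixing it in advance also prevents a choice of adjustment after the data are seen.
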